### 2.6. Intervention

BCI-based rehabilitation will be delivered using the recoveriX system (g.tec medical engineering GmbH, Austria), a commercially available FDA-approved BCI platform that has been validated in stroke and multiple sclerosis [28,37]. The recoveriX system integrates three key components: (1) a wet-electrode EEG head cap for neural signal acquisition, (2) signal processing software that automatically calibrates and decodes motor imagery patterns, and (3) a functional electrical stimulator (FES) that delivers peripheral muscle stimulation synchronized with detected motor intent [38].

**Training Protocol:** Participants will undergo up to 15 BCI rehabilitation sessions over 3–4 weeks (4–5 × 30 min sessions per week), supervised by trained therapists or clinical research assistants. Each session comprises three blocks of 80 trials (240 trials total). Individual trials follow a structured sequence (Figure 2): 2 s baseline period, auditory cue signaling trial initiation, 1 s delay, visual cue (animated arrow) with auditory instruction indicating whether to imagine left or right finger extension, followed by 5 s of motor imagery with real-time feedback. The motor imagery employed is kinesthetic, first-person imagery of a discrete, non-goal-directed movement—specifically, imagining the sensation of extending the fingers and opening the hand on the cued side—rather than goal-directed, object-oriented actions such as reaching to grasp an object. This reflects the validated two-class recoveriX paradigm and the need for a temporally precise, repeatable motor template that can be reliably decoded and synchronized with functional electrical stimulation; goal-directed, object-oriented practice is instead delivered during the subsequent conventional occupational therapy block. Motor imagery detection is assessed every 200 milliseconds; upon detection, the FES stimulates the forearm finger extensor muscles while an avatar on screen displays corresponding hand movement, providing multimodal sensory feedback [39].

**FES Parameters:** Electrode skin pads will be placed over the forearm finger extensor muscle groups. Electrical stimulation will be delivered at a pulse frequency of 50 Hz with a pulse width of 300 microseconds. Stimulation intensity (in milliamperes) will be individually titrated to produce visible wrist and/or finger extension without pain or muscle spasms.

**Concomitant Therapy:** Following each recoveriX session (approximately 30 min), participants will receive 60 min of standard-of-care conventional occupational therapy within 30–60 min of BCI training completion, resulting in a total therapy time of 90 min per session. This represents additional therapy (approximately 30 min) compared to standard care [40]. We acknowledge that as designed, this adjunctive schedule confounds the specific effect of closed-loop BCI neurofeedback with the effect of additional therapy time so that any functional gain cannot be attributed unambiguously to the brain–computer interface rather than to a greater rehabilitation dose. An adjunctive design was nonetheless chosen for pragmatic and ethical reasons in this acute inpatient population, in which withholding standard therapy in order to time-equate the arms would be inappropriate and the primary aim is feasibility rather than efficacy. To mitigate this confounder, we will (i) prospectively record the total upper limb therapy dose (in minutes and repetitions) for both BCI participants and historical controls, (ii) enter total therapy time as a covariate in exploratory effectiveness and cost analyses, and (iii) report the incremental cost of the additional therapist time separately from device-related costs. For the future definitive trial, a dose-matched (time-equated) active comparator—delivering an equivalent duration of conventional or sham/attention-controlled therapy—is planned so that the independent contribution of the closed-loop BCI can be isolated. Standard inpatient multidisciplinary stroke rehabilitation therapies will continue throughout the inpatient rehabilitation period. To prevent potential contamination of therapeutic effects, standard non-invasive upper limb FES over the forearm finger extensor muscle groups will not be applied during the inpatient stay where possible.

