### 3.5. Cost Perspective and Therapy Time Differential

The BCI intervention is modeled as additional adjunctive therapy in addition to standard of care rather than a substitute for standard care. Under this assumption (Scenario A), BCI participants receive 30 min of BCI training plus 60 min of standard occupational therapy per session (90 min total), whereas standard care patients receive approximately 60 min of occupational therapy per session based on TTSH rehabilitation protocols [40]. The incremental cost of BCI therefore includes both equipment-related costs and the additional 30 min of therapist time per session. Where available, actual billed charges from hospital administrative databases will be used to estimate healthcare costs. For intervention-specific costs not captured in routine billing (e.g., BCI equipment depreciation, additional therapist time), unit costs will be derived from institutional costing data. This pragmatic approach balances data availability with accuracy of cost estimation. A sensitivity scenario modeling partial substitution—approximately 25%, rather than 50%, of within-session supervision withdrawn from the midpoint of the training course following an initial supervised orientation period, noting this proportion may vary in practice—will be examined to explore conditions under which a favorable ICER may be achievable.

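### Standard forearm FES is withheld from BCI participants where possible, yet BCI is analysed as a pure addition to standard care; the exploratory contrast shifts to the extent that historical controls received such FES

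*Protocol article*

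**What the plan says.** All references are to the protocol article.

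- **Section 2.6, Concomitant Therapy.** The general rule is "Standard inpatient multidisciplinary stroke rehabilitation therapies will continue throughout the inpatient rehabilitation period". The sentence after it, aimed at preventing contamination, says "standard non-invasive upper limb FES over the forearm finger extensor muscle groups will not be applied during the inpatient stay where possible". Earlier in the same paragraph the adjunctive design is defended on the ground that "withholding standard therapy in order to time-equate the arms would be inappropriate".
- **Section 2.6, Training Protocol.** The BCI session itself delivers detection-triggered FES to the forearm finger extensors, the same muscle group.
- **Section 3.5.** BCI is modelled as "additional adjunctive therapy in addition to standard of care rather than a substitute for standard care". Participants have 30 min of BCI plus 60 min of occupational therapy, while "standard care patients receive approximately 60 min of occupational therapy per session based on TTSH rehabilitation protocols". The consequence drawn is: "The incremental cost of BCI therefore includes both equipment-related costs and the additional 30 min of therapist time per session". Table 2 repeats the 90 versus 60 min contrast.
- **Section 3.12.** The gain under standard rehabilitation at the hospital (29.1 to 37.4 points, +8.3) is added to the meta-analytic BCI change of 5.23 points, giving an expected total of about 13–14 points if effects add.
- **Section 3.3.** Controls come from the hospital's own rehabilitation cohort. The propensity model includes total inpatient therapy dose, concomitant medications and calendar year. It does not list FES exposure, and no FES restriction on controls is stated.

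**The concern.** The analysis sections describe the contrast as standard care plus BCI versus standard care. The intervention section takes out, as far as possible, one component that it labels standard. If the controls had that component, the comparison changes two things at once: BCI is added and conventional forearm FES is removed.

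This bears on every comparison that uses the controls or the standard-care gain: the ICER and cost per FMA-UE point (section 3.7), the benchmarking of FMA-UE and ARAT against matched controls (section 4), and the additive expectation (section 3.12).

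The safeguards in the article measure quantity of therapy. Section 2.6 records upper limb dose in minutes and repetitions for both groups and enters total therapy time as a covariate; section 3.3 matches on total dose. Neither shows whether the minutes included FES. The partial-substitution scenarios in sections 3.5 and 3.9 concern supervision. The stated limitations cover extra therapy time, historical and temporal confounding, and spontaneous recovery, but not the withheld FES. Because the restriction applies only where possible, exposure may also differ among the 12 participants.

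**Working it through.** **1. The plan's own figures reproduce under pure addition.**

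- Standard-rehabilitation gain: 37.4 − 29.1 = 8.3 points.
- Additive total: 8.3 + 5.23 = 13.53 points, inside the stated 13–14.
- Session time: 30 + 60 = 90 min; 90 − 60 = 30 min added.

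**2. What the contrast estimates once FES is withheld.** Let B be the effect of adding BCI, f the effect of standard forearm FES, and qc and qb the shares of controls and BCI participants given it. Then

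expected difference = B − (qc − qb) × f.

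The plan's reading needs (qc − qb) × f = 0. That holds if no one in either group had standard FES, if both groups had it equally, or if it has no effect.

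**3. Illustration.** The article gives none of qc, qb or f. B = 5.23 is the plan's expected BCI change; the rest is assumed. The total uses 8.3 + 5.23 and assumes that the cohort behind the 8.3 points had the same FES share qc. Cells show the difference from controls, then the total gain, in FMA-UE points with qb = 0.

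| qc | f = 1 | f = 2 | f = 3 |
|---|---|---|---|
| 0 | 5.23 / 13.53 | 5.23 / 13.53 | 5.23 / 13.53 |
| 0.25 | 4.98 / 13.28 | 4.73 / 13.03 | 4.48 / 12.78 |
| 0.50 | 4.73 / 13.03 | 4.23 / 12.53 | 3.73 / 12.03 |
| 1 | 4.23 / 12.53 | 3.23 / 11.53 | 2.23 / 10.53 |

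If a quarter of BCI participants still receive standard FES (qb = 0.25), the last row becomes 4.48, 3.73 and 2.98 for the difference. With qc also 0.25 the shift is zero. The total falls below 13 once (qc − qb) × f exceeds 13.53 − 13 = 0.53 points.

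**4. Therapy time.** If standard FES is given inside the 60 min of occupational therapy, total minutes are the same with or without it, so a time covariate cannot detect it. If it is given separately and takes m minutes per session (assumed 0 to 30), the net added time is 30 − m, that is 30 down to 0 min, instead of a fixed 30.

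**The case against.** The strongest reply is that the text states a rule and then a reasoned exception. In section 3.5 the denial of substitution is explained by the minutes that follow it: occupational therapy time is not replaced. In section 2.6 the refusal to withhold therapy concerns equalising time between arms. Leaving one modality out of an unchanged 60 min fits both statements. Moreover, standard FES may simply mean conventional FES not triggered by BCI, and the Background's list of current upper limb options does not name FES. This stands as a fair reading of the individual sentences. It does not make the contrast with controls one of pure addition if controls had FES, and the article does not say that they had none.

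Three stronger readings are tempting and are not supported:

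- **That controls did receive forearm FES, so the comparison is biased.** No section says so. The word standard suggests it without establishing it.
- **That the BCI effect is understated.** This needs qc > qb and a beneficial f, neither of which is given.
- **That the saving from withheld FES is left out of the costs.** Section 3.5 uses billed charges where available, and Table 2 counts total OT/PT sessions in both groups, so some FES cost may already be captured. FES given within the 60 min would save no therapist time.

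It is also true that the comparison is labelled exploratory, that residual confounding from historical controls is acknowledged, and that section 2.6 already concedes that gains cannot be attributed unambiguously to BCI. These points limit the weight of the concern. They do not tell a reader which contrast the ICER refers to.

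**Conclusion.** The point holds conditionally. Sections 3.5 and 3.12 treat BCI as pure addition, while section 2.6 withholds standard forearm FES where possible. To the extent that controls received it, the exploratory contrast is BCI plus standard care without standard FES versus standard care as delivered.

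The size is (qc − qb) × f and cannot be fixed from the article. It is zero if controls had no such FES, and runs from 0.25 to 3 points over the non-zero values of qc in the table with qb = 0. The table assumes that effects add and that FES acts alike in both groups.

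The primary feasibility endpoints use no controls and are unaffected. What changes is what the ICER, the cost per FMA-UE point and the benchmarking can claim. That makes this a correction worth making, because these results are meant to inform the definitive trial.

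**What to change.** 1. Reconcile sections 2.6, 3.5 and 3.12 on what is given alongside BCI. This takes no view on whether standard FES should be given.
2. Describe the contrast as delivered in the economic and benchmarking sections, and list the FES restriction among the limitations.
3. Extract standard forearm FES exposure (yes/no, number of sessions) from therapy records in both groups where available, and report it, including any given to BCI participants.
4. Add one exploratory sensitivity analysis by control FES exposure. State that FES is a post-baseline treatment whose use may reflect severity, so selecting controls on it can introduce its own bias; the result is a check and should not replace the main comparison.

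The cost is protocol wording, one extra extraction item, and a smaller control pool in that analysis. The pool matters: 1:3 matching for 12 participants needs up to 36 controls from a cohort of somewhat over 100.

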**BCI Performance Metrics:** Variables relating to recoveriX BCI system performance will be collected including motor imagery classification accuracy, BCI compatibility index, response times, and session-by-session variability in decoding performance. These metrics will provide insight into the reliability of the BCI system in this patient population and potential predictors of clinical response. These technical metrics constitute a primary feasibility domain and are defined a priori as follows. Motor imagery classification accuracy is the proportion of cued trials in which the online classifier correctly identifies the intended (left or right) hand for the two-class paradigm, computed per session; a session is considered to demonstrate adequate BCI control when accuracy exceeds the participant-specific permutation-derived chance level and meets the conventional binary BCI control benchmark of at least 70%. The true positive rate is the proportion of cued trials in which motor imagery is detected and triggers functional electrical stimulation on the correct side. The BCI compatibility index is the recoveriX system index of how reliably a participant’s motor imagery can be decoded. Session-to-session reliability is the within-participant variability in classification accuracy across the training course. At the cohort level, we will report the proportion of participants achieving the 70% accuracy benchmark (a measure of BCI literacy in acute and subacute stroke) and the trajectory of accuracy over successive sessions.

### 3.1. Signal Acquisition and Processing

EEG signals will be recorded throughout each therapy session using the recoveriX system’s integrated amplifier (g.USBamp) via 11 active wet electrodes positioned over sensorimotor cortex (10–20 system: FC3, FCz, FC4, C3, C1, Cz, C2, C4, CP3, CPz, CP4, and additional reference channels), sampled at 256 Hz with online 0.5–30 Hz bandpass and 50 Hz notch filtering. In addition, and in response to reviewer feedback, two occipital derivations (O1 and O2) will be recorded where the amplifier channel configuration permits so that the dominant posterior (alpha) rhythm can be monitored continuously as an on-line index of arousal. This is important because early post-stroke patients frequently exhibit fluctuating vigilance (drowsiness or stupor), which can confound an attention-dependent motor imagery paradigm; trials or sessions recorded during posterior-rhythm-confirmed drowsiness will be flagged and, where appropriate, excluded from efficacy analyses (see quality-control pipeline below). Given that the inclusion criterion of MoCA > 20/30 and exclusion of participants with disorders of consciousness or altered arousal states already limit enrollment of patients prone to clinically significant drowsiness, this concern is expected to be largely mitigated at the eligibility stage; posterior-rhythm monitoring is retained as an additional session-level safeguard. Post hoc signal processing will be performed using Python with established neuroscientific analysis packages. Processing pipeline will include frequency filtering (bandpass filters isolating delta, theta, alpha/mu, beta, and gamma bands), spatial filtering using Common Spatial Pattern algorithms, and feature extraction for machine learning analysis [42]. We will employ Linear Discriminant Analysis (LDA) and/or other classification approaches to identify electrophysiological features correlated with motor recovery trajectories. CSP+LDA was selected, as it is the validated reference pipeline within recoveriX and remains robust at the small per-session sample sizes typical of clinical BCI use. Successful motor imagery generation will be verified per session via the recoveriX BCI compatibility index and cross-validated classification accuracy against permutation-derived chance level, with FES triggered only when the classifier detects motor imagery for the cued side. To address EEG contamination from concurrent FES, stimulation epochs will be excluded from online classifier updates, and offline analyses will apply standard stimulation-artifact removal (notch filtering at the stimulation frequency and its harmonics, with ICA-based rejection of stimulation-locked components).

To standardize electrophysiological data quality and support reproducibility, a pre-specified signal quality-control and preprocessing pipeline will be applied. Prior to every session, electrode–skin impedance will be verified and maintained below 10 kΩ (target < 5 kΩ) for all active electrodes, with re-gelling or re-seating of electrodes and re-testing until this threshold is achieved; impedance values will be logged for each session. Continuous EEG will be segmented into cue-locked epochs, and a uniform artefact-handling pipeline will comprise (i) band-pass (0.5–30 Hz) and 50 Hz notch filtering; (ii) automated rejection of epochs exceeding ±100 µV or containing flat or saturated (railing) segments; (iii) independent component analysis (extended Infomax) with removal of components classified as ocular (blink or saccade), electromyographic, electrocardiographic, or functional-electrical-stimulation-locked artefact, using a combination of an automated classifier (for example ICLabel) and blinded expert visual review; and (iv) exclusion of any session in which fewer than 60% of cued trials survive artefact rejection or in which the posterior alpha rhythm indicates sustained drowsiness. All data exclusions and their reasons will be pre-specified and reported transparently to support reproducibility of the electrophysiological biomarker analyses.

A priori electrophysiological biomarkers of motor recovery, and their association with clinical change, will be defined and tested in a pre-specified manner. The primary candidate biomarkers are (i) the magnitude of event-related desynchronization and synchronization (ERD/ERS) in the contralesional and ipsilesional mu (8–13 Hz) and beta (13–30 Hz) bands during motor imagery; (ii) the hemispheric laterality index of sensorimotor ERD; (iii) the CSP-LDA classification accuracy and its session-to-session trajectory; and (iv) the recoveriX BCI compatibility index. The principal clinical anchor will be the change in FMA-UE from baseline to week 3–4, with change in ARAT as a secondary anchor. For each biomarker, both the baseline value and the within-training slope will be related to clinical change using Spearman rank correlation coefficients and, where the sample permits, robust linear regression adjusting for baseline motor severity, with 95% confidence intervals reported throughout. Given the exploratory sample size, these biomarker–outcome associations are explicitly hypothesis-generating; they will be interpreted descriptively, with Benjamini–Hochberg control of the false discovery rate, rather than as confirmatory tests, and will be used to nominate candidate predictive biomarkers for a future definitive trial.

As an exploratory predictor of treatment response and following reviewer suggestion, sensorimotor ERD will additionally be recorded during a brief action-observation task at baseline, in which the participant watches a filmed version of the to-be-performed hand movement. Motor imagery and action observation engage a largely shared frontoparietal network—the putative human mirror mechanism [43]—and a robust ERD elicited while observing a to-be-performed action has been associated with a favorable response to motor rehabilitation after stroke [44,45]. Baseline action-observation ERD will therefore be examined as a candidate stratifying biomarker and, potentially, as an eligibility-refining criterion for a future definitive trial rather than as a mandatory enrolment criterion in the present feasibility study.

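### A gamma band is to be isolated for exploratory recovery models from EEG that the plan band-passes at 0.5–30 Hz, so gamma features could not be read as gamma activity

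*Protocol article*

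**What the plan says.** All the relevant text is in section 3.1 (Signal Acquisition and Processing) of the protocol article.

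- **Recording.** EEG is "sampled at 256 Hz with online 0.5–30 Hz bandpass and 50 Hz notch filtering".
- **Offline pipeline.** To standardise data quality, "a uniform artefact-handling pipeline will comprise (i) band-pass (0.5–30 Hz) and 50 Hz notch filtering", followed by amplitude-based epoch rejection, independent component analysis and session-level exclusions.
- **Band isolation.** Post hoc processing includes "bandpass filters isolating delta, theta, alpha/mu, beta, and gamma bands", then spatial filtering and feature extraction. Linear discriminant analysis or other classifiers are then used "to identify electrophysiological features correlated with motor recovery trajectories".
- **Band edges.** The primary candidate biomarkers use "mu (8–13 Hz) and beta (13–30 Hz) bands during motor imagery". No limits are given for gamma.
- **Stimulation artefact.** Offline analyses add "notch filtering at the stimulation frequency and its harmonics" and remove stimulation-locked components. Section 2.6 sets the FES pulse frequency at 50 Hz.

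Nothing in the article exempts gamma from either band-pass or describes a separate wide-band recording or analysis branch.

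**The concern.** With beta ending at 30 Hz, gamma is what lies above 30 Hz, and both stated filters are designed to remove exactly that range. The plan then isolates the removed range and passes features from it to models that look for correlates of recovery.

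Attenuation does not make such a feature harmless. Standard linear discriminant analysis is unaffected by rescaling a feature, so a band reduced to a small fraction of its power can still enter with full influence. Any result would be labelled gamma, although the quantity measured would be mainly the edge of the filter just above beta. The stake is the interpretability of one of the five listed bands in an exploratory analysis, and the reproducibility that the pre-specified pipeline is meant to secure.

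**Working it through.** **Step 1: set the stated limits side by side**

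| Item | Range | Source |
|---|---|---|
| Online band-pass | 0.5–30 Hz | section 3.1, recording |
| Offline band-pass | 0.5–30 Hz | section 3.1, quality-control pipeline |
| Beta | 13–30 Hz | section 3.1, candidate biomarkers |
| Gamma | above 30 Hz | follows from the beta limit |
| Nyquist frequency | 256 / 2 = 128 Hz | sampling rate in section 3.1 |

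The overlap of gamma with either pass-band is nil apart from filter roll-off. Sampling rate is not the constraint, because 128 Hz is well above 30 Hz. The filters are the constraint.

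**Step 2: how much survives the roll-off**

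The plan gives no figure to reproduce. Filter type and order are not stated, so Butterworth 0.5–30 Hz band-pass filters of design order 2, 4 and 8 at 256 Hz are assumed, with the 50 Hz notch applied in each pass and a 1/f spectrum. With H(f) the filter response, including the notch, and k the number of passes:

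- gain at f in dB = k × 10·log10(|H(f)|²)
- share of 30–100 Hz power kept = Σ |H(f)|^(2k)·(1/f) ÷ Σ (1/f), summed over frequencies above 30 Hz up to 100 Hz

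One online plus one offline pass (k = 2):

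| Design order | Gain at 40 Hz | Gain at 60 Hz | Share of 30–100 Hz power kept | Part of that from 30–35 Hz |
|---|---|---|---|---|
| 2 | −13.7 dB | −30.5 dB | 3.2% | 66% |
| 4 | −23.8 dB | −60.3 dB | 1.6% | 89% |
| 8 | −46.5 dB | −120.6 dB | 0.7% | 99% |

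In power terms, 40 Hz is reduced to 10^(−1.37) = 4.3%, 10^(−2.38) = 0.42% and 10^(−4.65) = 0.002% of its original level.

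**Step 3: vary the number of passes**

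| Filtering | Order 2 | Order 4 | Order 8 |
|---|---|---|---|
| Online only | 11.2% | 5.8% | 2.8% |
| Online + one offline pass | 3.2% | 1.6% | 0.7% |
| Online + zero-phase offline (two passes) | 1.1% | 0.5% | 0.2% |

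Even the most favourable case, the online filter alone at the shallowest order, keeps about 11% of the power, of which 46% lies at 30–35 Hz. Under every filtering chain that the text describes, the gamma feature is a strongly attenuated signal weighted towards the frequencies just above beta.

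**The case against.** The strongest defence is that the online filter may serve only the classifier stream, with raw data also stored. The article separates online from post hoc processing and does not say that only filtered data are kept. Planning offline notches at harmonics of 50 Hz would also make little sense on data already cut at 30 Hz. Storage and per-band branches are details that a condensed article may leave to the full protocol. This part stands as a possibility. It does not remove the point: the offline band-pass has the same 30 Hz limit, belongs to a pipeline called uniform, and exempts no gamma branch. The article fixes the cut-off twice and names the band, so a later document cannot honour both statements without changing one.

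Four stronger readings that a reader might draw are not supported:

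- **Gamma would be nominated as a biomarker.** The primary candidates are mu and beta ERD/ERS, ERD laterality, decoding accuracy and the compatibility index. Gamma is not among them, and nomination is described for the listed associations.
- **Gamma adds false positives or weakens the false-discovery-rate control for mu and beta.** The baseline-and-slope correlations apply to the listed biomarkers. No gamma tests are planned within that family.
- **The features would track stimulation residue.** The plan includes stimulation-frequency and harmonic notches, component removal and blinded expert review. The calculation above concerns filter gain only and does not show that stimulation artefact survives.
- **No cortical signal at all could remain.** A shallow filter leaves an attenuated skirt at 30–35 Hz.

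**Conclusion.** The point holds as an internal contradiction of low severity. The plan names an analysis that its own filters cannot support. Followed as written, it yields gamma features carrying roughly 0.7% to 3.2% of the original 30–100 Hz power, mostly from 30–35 Hz, and these could not be interpreted as gamma activity.

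The percentages rest on assumed Butterworth filters, orders 2 to 8, and a 1/f spectrum. The contradiction itself rests only on the stated 30 Hz limits. The effect is confined to the exploratory machine-learning feature set, and the article describes its biomarker–outcome work as hypothesis-generating. The named biomarkers, feasibility endpoints and clinical outcomes are unaffected.

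**What to change.** Choose one of two changes to section 3.1.

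1. **Delete gamma from the band list**, so that every feature lies within 0.5–30 Hz. This costs one word. Exploratory gamma results are given up, but the stated filters could not have supplied interpretable ones.
2. **Keep gamma and make it measurable.** State before recording starts that unfiltered 256 Hz data are stored, because signal removed at acquisition cannot usefully be recovered. Define a separate wide-band offline branch with explicit gamma limits, handling of 50 Hz mains and FES interference, and restriction to stimulation-free epochs. The cost is extra storage, a second preprocessing branch and fewer usable epochs for that band.

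The first option is the proportionate one unless gamma is of real interest. Neither option changes an endpoint or the sample size.

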### 2.3. Eligibility Criteria

**Inclusion criteria are as follows:** adults aged 21–80 years with confirmed hemorrhagic or ischemic stroke on neuroimaging, stroke onset within 2–12 weeks; demonstrated voluntary finger flexion or extension by Oxford Medical Research Council (MRC) grade 0–4/5, Montreal Cognitive Assessment (MoCA) score > 20/30; ability to understand written and spoken instructions; and stable medical and neurological status as determined by the clinical team [34]. Because the closed-loop paradigm depends on integrating afferent (proprioceptive and visual) feedback with efferent motor intent, lesion location will be documented from neuroimaging; participants with predominantly cerebellar or brainstem lesions—who may retain intact primary sensation yet have impaired updating of internal sensorimotor (forward) models, that is, impaired predictive coding—will remain eligible but will be flagged a priori. For such participants the intervention explicitly leverages the multimodal, error-corrective feedback intrinsic to the recoveriX loop (synchronized FES-evoked movement together with visual avatar feedback) as an externally supplied source of sensory prediction; their decoding performance and clinical response will be examined as an exploratory subgroup to determine whether impaired predictive coding attenuates BCI benefit and should inform eligibility for a future definitive trial. Because the motor-imagery-related event-related desynchronization (ERD) used for BCI classification is recorded over central sensorimotor electrodes (FC3–CP4) rather than posterior/occipital sites, cerebellar lesions are not expected to directly impair this signal; ERD magnitude and BCI performance in this subgroup will nonetheless be examined exploratively as above.

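### ERD/ERS magnitude is labelled by lesion side although cerebellar and brainstem strokes are eligible, so the label can be reversed or undefined relative to the paretic arm (minor point)

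*Protocol article*

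**What the plan says.** Section 3.1 lists four primary candidate biomarkers:

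- Biomarker (i) is a size measure for each hemisphere, labelled by lesion side: "ERD/ERS) in the contralesional and ipsilesional mu (8–13 Hz) and beta (13–30 Hz) bands during motor imagery".
- Biomarker (ii) is an asymmetry measure whose orientation is not given: "the hemispheric laterality index of sensorimotor ERD".
- Biomarker (iii) is a decoding measure with no lesion-side label: "the CSP-LDA classification accuracy and its session-to-session trajectory".
- Biomarker (iv) is a device score, again without a lesion-side label: "the recoveriX BCI compatibility index".

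The baseline value and within-training slope of each are related to FMA-UE change (ARAT change as secondary anchor) by Spearman correlation. Where the sample permits, a robust regression adjusts for baseline motor severity. The section calls these associations hypothesis-generating and intends them to nominate predictors for a definitive trial.

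Section 2.3 (Eligibility Criteria) names "participants with predominantly cerebellar or brainstem lesions" as a group of interest. It states that they "will remain eligible but will be flagged a priori". On their analysis it adds that "their decoding performance and clinical response will be examined as an exploratory subgroup". It also argues that a cerebellar lesion should not directly impair the central ERD signal. Section 3.12 (Data Analysis) summarises outcomes by lesion location, descriptively only.

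**The concern.** The biomarker is indexed by the side of the lesion, while the outcome is indexed by the side of the weak arm. In a hemispheric stroke the two agree: the ipsilesional sensorimotor cortex is the one opposite the paretic arm. A lesion of one cerebellar hemisphere affects the arm on the same side (general anatomy, not stated in the article). The cortex opposite that arm is then contralesional, and the value entered as ipsilesional belongs to the unaffected arm. A midline or bilateral brainstem lesion has no lesion side, so biomarker (i) cannot be assigned.

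One variable name would then hold different physiological quantities in different participants. Pooling them pulls the correlation towards zero. At stake is the stated use of the result: section 4 (Discussion) carries these biomarkers forward as pre-specified candidate predictors. Relabelling after the data are seen would undercut that pre-specification.

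**Working it through.** The article states no correlation or power for this analysis, so there is no figure to reproduce. The check has two parts.

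**1. Does any text repair the label?**
- Section 2.3 flags the participants and examines their decoding, ERD magnitude and clinical response as a subgroup. Its reasoning on cerebellar lesions covers whether the signal is intact, not which hemisphere carries which label.
- Section 3.1 adjusts for baseline motor severity, not lesion location.
- Section 3.12 gives descriptive summaries by location.

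None of these relabels the participants, excludes them from the pooled association, or ties the hemisphere to the paretic hand.

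**2. How large is the effect?**

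Input from the article: n = 12 (section 2.4). Assumptions: true correlation ρ = 0.5 or 0.7; inter-hemispheric correlation r = 0 or 0.5; mean difference between hemispheres 0 or 1 SD; k = 0 to 3 participants with swapped labels.

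Model: A is ERD in the hemisphere opposite the paretic arm, C = rA + √(1 − r²)·e₁ (plus the mean difference) is ERD in the other hemisphere, and clinical change is y = ρA + √(1 − ρ²)·e₂. In k participants C is entered in place of A. Mean Spearman coefficient over 20,000 simulated samples, with ranges over r and the mean difference:

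| k | Biomarker (i), ρ = 0.5 | Biomarker (i), ρ = 0.7 |
|---|---|---|
| 0 | 0.45 | 0.64 |
| 1 | 0.40–0.43 | 0.57–0.61 |
| 2 | 0.36–0.41 | 0.51–0.58 |
| 3 | 0.32–0.39 | 0.45–0.56 |

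Loss at k = 1: 0.45 − 0.43 = 0.02 up to 0.64 − 0.57 = 0.07. Loss at k = 3: 0.45 − 0.39 = 0.06 up to 0.64 − 0.45 = 0.19.

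Hand check at zero mean difference: the coefficient is multiplied by roughly 1 − (k/n)(1 − r). For k = 3 this is 0.75 at r = 0 and 0.875 at r = 0.5. So 0.45 × 0.75 = 0.34 and 0.45 × 0.875 = 0.39, matching the simulated 0.34 and 0.39.

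A laterality index A − C oriented by lesion side changes sign in a reversed participant, so the multiplier is about 1 − 2k/n, or 0.5 at k = 3. Simulated values from k = 0 to k = 3 fall from 0.31 to 0.16 or 0.22 to 0.11 (ρ = 0.5), and from 0.45 to 0.22 or 0.31 to 0.16 (ρ = 0.7).

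For scale, the approximate 95% interval for an observed Spearman coefficient of 0.5 at n = 12 uses SE = √((1 + 0.5²/2)/9) = 0.354 on the Fisher scale. That gives tanh(0.549 ± 1.96 × 0.354), or about −0.14 to 0.85.

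**The case against.** The strongest reply is that little depends on this. The associations are exploratory, described as such and controlled for false discovery. No feasibility, safety or economic result rests on them, and with 12 participants the interval is far wider than the loss from one swapped label. The flag in section 2.3 would let an analyst notice and correct a reversal. The finger-strength criterion (MRC grade 0–4) also keeps out a cerebellar stroke with full finger power, so the number affected may be zero. All of this stands, and it limits the size of the point. It does not make the label correct for a group that the article expressly admits.

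A reader might infer more than the text supports:

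- **That the EEG biomarkers as a whole are compromised.** Only (i) carries a lesion-side label. The orientation of (ii) is not stated. (iii) and (iv) do not depend on it.
- **That the biomarker's sign flips.** For (i) a wrong label substitutes the other hemisphere's value. Sign reversal, with its larger loss, applies only to a lesion-oriented laterality index.
- **That one to three reversed participants should be expected.** The article gives no expected number. Brainstem lesions may agree with the label, reverse it or leave it undefined.
- **That lateralised ERD cancels because both hands are cued.** Sessions do use a cue "indicating whether to imagine left or right finger extension" (section 2.6), but nothing says ERD is averaged over both cues, and epochs are cue-locked. Which trials enter the estimate is a detail that an article may leave to the full protocol or analysis plan. Averaging would in any case not cancel a per-hemisphere magnitude.

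**Conclusion.** The point holds as a minor one. Followed as written, section 3.1 mislabels the hemisphere in a unilateral cerebellar participant and leaves the label undefined in a midline or bilateral brainstem lesion. The direction is attenuation in every scenario examined. Under the assumptions above the loss for biomarker (i) is small with one swapped participant and moderate with three; the halving of a laterality index is conditional on an orientation that the article does not give. The label conflict follows from the text and basic anatomy. The size rests on assumed correlations and on an assumed number of such participants.

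**What to change.** In section 3.1, define the hemispheres for biomarker (i), and the orientation of the laterality index (ii), as contralateral versus ipsilateral to the paretic hand. This leaves hemispheric strokes labelled as now and corrects the cerebellar ones. It also gives a defined value for a midline or bilateral brainstem lesion, provided that one arm is paretic. Add one sensitivity analysis that repeats the pooled association without the flagged cerebellar and brainstem participants. The cost is a change of wording and one extra run. No new data are needed, since the flag is already planned and the paretic side is known from the clinical assessment.

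As an optional clarification, not the correction of a stated error, the section could say that (i) and (ii) use paretic-hand-cued trials, with the other trials reported separately. If cues are split evenly between hands, that leaves about 240 / 2 = 120 trials per session for these two measures.
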